### Outcomes

A theory of change was developed with input from BRAC to identify the anticipated outcomes of STAR+. The ultimate aim of STAR+ is to improve opportunities for decent work amongst youth with disabilities, which can lead to reduced poverty and improved participation and well-being. The primary outcome measures are employment and earnings (Table 1). Secondary outcome measures will include household poverty and the participant’s subjective well-being, social participation/empowerment and experiences of stigma and discrimination. Indicators are tied to the SDGs where possible.

Furthermore, the endline survey will collect information from the intervention arm about their experience participating in the programme, including (a) details on receipt of different components of the intervention to explore fidelity and uptake (e.g. what was received, frequency, how delivered); (b) satisfaction with the programme overall and with specific components; (c) challenges experienced during any component of the intervention; and (d) self-reported impacts of participation.

### Sample size

Sample size calculations were conducted in R using the ‘clusterPower’ package. The programme will work with approximately 750 learners in 45 of the 91 eligible BRAC branch offices; we have therefore assumed that each branch could work with 16 learners (1500/91). Sample size calculations are based on the primary outcome of the proportion of learners in employment. The possible effect size was calculated using the proportion in employment in the STAR evaluation (53%) and the proportion in the control (41%). For the proportion in the control, an ‘exclusion factor’ of between 0 and 50% was applied to reflect the various probabilities that the employment amongst those eligible for STAR+ will be lower than what was observed amongst STAR participants. As the level of clustering is unknown, the study power was estimated for a range of values.

The results of the sample size calculations are shown in Fig. 1. Each line shows the number of clusters required in each arm to achieve 80% power for different levels of employment in the control arm and for different intraclass correlation coefficients (ICCs). When the ICC is low (0.1), the trial will have sufficient power for up to and including a control-arm proportion equal to that observed in the STAR trial. For a more conservative ICC of 0.2, the trial will be sufficiently powered when the control arm has 95% of the employment seen in STAR. As the ICC increases, the power is reduced, however with an ICC of 0.4 — representing high levels of clustering — the trial will still be sufficiently powered so long as the employment in the controls is approximately 75% of that observed in STAR. Since we expect that there is a substantial effect of disability on employment in this context, we consider this to be adequately powered.

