## Methods and analysis

### Design

The study’s main design is a multicentre, superiority cRCT. BRAC’s 91 branch office catchment areas will serve as the clusters for this trial. These clusters cover 39 of the 64 districts of Bangladesh. Of the 91 branches, 45 have been randomly allocated to being implementers of STAR+. The remainder of the branches will serve as control areas and will not implement STAR+ during the study timeframe. Control areas may implement other livelihood programmes (e.g. 15 were randomly allocated to implement standard STAR). BRAC has identified youth with disabilities meeting the STAR+ eligibility criteria in both the control and intervention clusters. Baseline data collection was collected after randomisation but before participants were invited to enrol in STAR+ to minimise anticipatory behaviour. Follow-up will be conducted 17 months after the completion of the delivery of STAR+ (24 months after baseline).

The cRCT will be complemented with qualitative research and a process evaluation. For the qualitative, in-depth interviews will be conducted with participants in both study arms at baseline and endline to explore their experiences of employment, and for the intervention arm, of the STAR+ programme. For the process evaluation, in-depth interviews with programme implementers will be conducted and monitoring data from BRAC and the endline of the cRCT will be reviewed to explore the implementation fidelity, mechanisms of impact, and contextual factors that can affect variations in outcomes. It will use the Medical Research Council guidance for process evaluations of complex interventions as a framework [17]. Researchers from the International Centre for Evidence in Disability at the London School of Hygiene & Tropical Medicine in the UK and the BRAC Institute of Governance and Development in Bangladesh will jointly design and implement the research.

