In-depth interviews will be conducted with 15-20 participants of the cRCT at endline, and with 15-20 programme implementers as part of the process evaluation. Interviews will use semi-structured topic guides and will be conducted by experienced researchers. They will be recorded, transcribed and translated to English. Interviews with cRCT participants will focus on barriers and enablers to seeking and retaining work and experiences on the job. STAR+ enrolees will also be asked about the perceived impact (if any) of the programme, the strengths and areas for improvement in different components to the programme, and any recommendations for adapting the overall programme. Interviews with implementers will focus on their experience developing and/or delivering the components of STAR+ they were responsible for, including any challenges, adaptations and suggestions for improvements.

Participants will be asked for multiple modes of contact during baseline to increase the response rate at endline.

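### The ICC 0.2 power statement falls about 3 points short of 80% on the printed inputs, and none of the power figures allow for loss by 24 months or for unequal branch sizes

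*Protocol article*

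**What the plan says.** The calculation is in the Sample size section of the protocol article. It takes employment of 53% from the STAR evaluation and 41% in the control, and scales only the control figure down by a factor of up to 50%. On cluster size it says "we have therefore assumed that each branch could work with 16 learners (1500/91". The power criterion comes with the description of the plotted results: "Each line shows the number of clusters required in each arm to achieve 80% power for different levels of employment in the control arm".

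Three statements follow.

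- ICC 0.1: "the trial will have sufficient power for up to and including a control-arm proportion equal to that observed in the STAR trial".
- ICC 0.2: "the trial will be sufficiently powered when the control arm has 95% of the employment seen in STAR".
- ICC 0.4: power is called sufficient with control employment at approximately 75% of STAR's.

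The section then judges the trial adequately powered, because disability is expected to lower employment substantially. It gives no alpha, sidedness, loss rate or variation in branch size. The Design and Timeline sections place endline about 24 months after baseline. The Data collection section says "Participants will be asked for multiple modes of contact during baseline to increase the response rate at endline".

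**The concern.** The ICC 0.2 sentence can be checked from its own inputs, and it does not reach 80%. Readers will use the three statements to judge how close control employment may come to STAR's before the trial is underpowered, so a threshold set too high gives false comfort where the effect is smallest.

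The calculation also treats everyone identified as if they will be analysed, in branches of identical size. Over 24 months some non-response is likely, and the retention measure shows that the authors have it in mind. People found door to door in branch catchment areas are unlikely to fall evenly across branches. Both features lower power, and the margin at ICC 0.1 is under 3 points.

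**Working it through.** **Inputs.** From Sample size: p1 = 0.53; p2 = 0.41 × f, where f is the fraction of STAR employment; n = 16 per branch; target power 80%. From Design: 45 intervention and 46 control branches (45 per arm is used below, then the actual split). Assumed, because not stated: two-sided alpha of 0.05, z = 1.960.

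**Formula.** Design effect DE = 1 + (n − 1) × ICC. With k branches per arm, SE = √[(p1(1 − p1) + p2(1 − p2)) × DE / (k × n)], and power = Φ((p1 − p2)/SE − 1.960).

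**The three statements, k = 45, n = 16**

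| ICC | f | p2 | DE | SE | (p1 − p2)/SE | Power |
|---|---|---|---|---|---|---|
| 0.1 | 1.00 | 0.4100 | 2.5 | 0.0413 | 2.906 | 82.8% |
| 0.2 | 0.95 | 0.3895 | 4.0 | 0.0520 | 2.702 | 77.1% |
| 0.4 | 0.75 | 0.3075 | 7.0 | 0.0670 | 3.320 | 91.3% |

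The first and third meet 80%. The second does not.

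**Branches needed at ICC 0.2, f = 0.95.** k = (1.960 + 0.842)² × (0.2491 + 0.2378) × 4 / (16 × 0.1405²) = 7.849 × 0.4869 × 4 / (16 × 0.01974) = 48.4, so 49 per arm. The pooled-variance, Fleiss and t versions, and adding one cluster as in Hayes–Moulton, give 50.

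**Does the method matter?** At ICC 0.2 and f = 0.95:

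- pooled variance or t: 76.2%
- Fleiss: 76.5%
- arcsine: 76.5%
- actual 45/46 split: 77.5%
- 45/46 split with the unrounded 16.48 per branch: 77.8%

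None of these two-sided versions reaches 80%.

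**Where the 80% boundary lies, k = 45, n = 16.** At ICC 0.2 it is f = 0.937 (0.933 with pooled variance or t), which is control employment of about 38.4%. At ICC 0.4 it is f = 0.829 (0.820 to 0.824).

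**Loss and unequal branches.** The documents give neither figure, so these are assumed values. Loss replaces n by m = 16 × (1 − loss), and DE becomes 1 + ((1 + CV²)m − 1) × ICC.

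| Assumed loss | Assumed CV | Power, ICC 0.1, f = 1 | Power, ICC 0.2, f = 0.95 |
|---|---|---|---|
| 0 | 0 | 82.8% | 77.1% |
| 10% | 0 | 81.3% | 76.2% |
| 15% | 0 | 80.5% | 75.7% |
| 20% | 0 | 79.5% | 75.1% |
| 0 | 0.3 | 80.7% | 74.2% |
| 10% | 0.3 | 79.2% | 73.3% |
| 20% | 0.4 | 75.9% | 70.2% |

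**Further from the boundary.** At ICC 0.2 with no loss and equal branches, power is 87.5% at f = 0.90 and 97.7% at f = 0.80.

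**The case against.** Several points on the other side have force.

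- **Alpha is not stated.** A one-sided 5% test would give 85.5% at ICC 0.2. That stands as a caveat, which is why the 77% is conditional on a two-sided 5% test. The article calls the trial a superiority trial but nowhere says that the test is one-sided.
- **Rounding could close the gap.** Unrounded values of 53.3% and 40.7% would give 80.4%, and the range consistent with the printed whole percentages is 70.9% to 82.5%. The 95% may also have been read off Fig. 1, which is not available here. So the shortfall is one on the printed inputs, and it is small: the boundary differs from the stated value by about half a percentage point of control employment (38.4% against 38.95%).
- **Loss and CV are not in the article.** This is right, and a condensed article may leave an allowance for loss to the full protocol. Those rows are a sensitivity range only. Loss of 10% or 15% alone leaves ICC 0.1 above 80%.
- **Adequacy does not rest on the 95% point.** This stands too. The authors expect control employment well below STAR's, where power is comfortable.

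A reader might go further and infer that the power thresholds as a set do not reproduce, or that the ICC 0.4 figure is an error in the opposite direction. The text does not support that. The ICC 0.1 statement is met, and the ICC 0.4 sentence offers approximately 75% as a sufficient condition, not as the exact boundary, so it is true and conservative. A reader might also infer that the trial is underpowered. That does not follow, because it depends on a control employment rate and an ICC that the section treats as unknown.

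**Conclusion.** One of the three power statements is not met on its printed inputs. At ICC 0.2 with control employment at 95% of STAR's, power is about 77% instead of at least 80%, assuming a two-sided 5% test. The corresponding threshold is about 94%.

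Separately, every figure in the section is for complete follow-up of 1500 people in equal branches. At ICC 0.1 the margin above 80% is lost at an assumed 20% loss, or at 10% loss with a CV of 0.3, but not at 10% or 15% loss alone. The true loss and CV are unknown from the article.

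This is a correction to a stated figure and a request for a more realistic one. It does not overturn the adequacy conclusion where control employment is well below STAR's, though the 87.5% at 90% of STAR is itself before any loss or branch-size variation.

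**What to change.** 1. State alpha and whether the test is one- or two-sided.
2. If it is two-sided 5%, change the ICC 0.2 threshold to about 94% of STAR employment, or keep 95% and give the power as about 77%. If unrounded inputs or another option produced the 95%, print them.
3. Optionally add that the 80% boundary at ICC 0.4 is about 83%. The present sentence need not change.
4. Restate power for the expected endline sample, using a stated loss rate (for example 10% to 20%) and the branch sizes already known from the 1500 identified people, with DE = 1 + ((1 + CV²)m − 1) × ICC, where m is the mean number per branch expected at endline.

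The cost is a recalculation and some rewording. No participants or branches are added, and no analysis changes. The one downside is that the stated power becomes slightly less favourable.

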The proposed study is a cluster randomised controlled trial (cRCT) of the STAR+ programme in Bangladesh. STAR+ is a skills development and job placement programme targeted to out-of-school youth with disabilities living in poverty, which is being run by the non-governmental organisation (NGO) BRAC and other partners in multiple districts of Bangladesh. The STAR+ programme is an adaptation to an existing livelihoods programme (STAR), which has been delivered to over 60,452 youth, including 6973 people with disabilities (11% of total graduates) as of May 2021. A previous RCT of STAR amongst the general population in Bangladesh found that key components of the programme increase labour market participation by 16 percentage points and earnings by 23% [16]. These effects were particularly pronounced amongst women. However, programme implementers have acknowledged that STAR required further adaptations to better support the inclusion of people with disabilities, as people with disabilities have been over-represented amongst the programme’s dropouts and typically only people with mild impairments have been included. Consequently, STAR+ was developed to address the gaps of STAR to improve employment opportunities amongst youth with disabilities.

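### The disability exclusion factor lowers only the control rate while STAR+ stays at 53%, so the power claims at ICC 0.2 and above rest on an effect that grows without justification

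*Protocol article*

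**What the plan says.** All of this is in the Sample size section of the protocol article unless another section is named.

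- Starting values: "the proportion in employment in the STAR evaluation (53%) and the proportion in the control (41" per cent), a difference of 12 points.
- Adjustment for disability: "For the proportion in the control, an ‘exclusion factor’ of between 0 and 50% was applied to reflect the various probabilities". The expectation behind it concerns everyone who qualifies for the programme, namely: "the employment amongst those eligible for STAR+ will be lower than what was observed amongst STAR participants". The text mentions no reduction of the 53%.
- Size: "we have therefore assumed that each branch could work with 16 learners (1500/91"). The Design section adds: "Of the 91 branches, 45 have been randomly allocated to being implementers of STAR"+, which leaves 46 control branches.
- Claims of at least 80% power: at ICC 0.1 with an unreduced control rate; at ICC 0.2 with controls at 95% of the STAR figure; and at ICC 0.4, where "the trial will still be sufficiently powered so long as the employment in the controls is approximately 75% of that observed in STAR".
- Conclusion: "Since we expect that there is a substantial effect of disability on employment in this context, we consider this to be adequately powered".

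The ICC is said to be unknown. Significance level and sidedness are not stated.

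**The concern.** The Eligibility criteria section requires participants in both arms to meet the same STAR+ criteria. If disability lowers employment among the eligible, it does so in both arms before any treatment effect. The calculation lowers one arm only, so each further step of assumed disadvantage is added to the treatment effect. The text gives no reason why youth with disabilities offered STAR+ would still reach the employment rate of a general-population STAR trial.

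This is the only power justification in the article, and its last sentence presents a large disability effect as the reason why power is adequate. A reader who accepts it could take a null employment result as evidence against an effect of the size seen in STAR, when at moderate clustering the trial may have had little chance of detecting one.

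**Working it through.** **Inputs.** 45 clusters per arm (Design; the control arm has 46, and using 45 changes little); 16 participants per cluster, 53% and 41% (Sample size). Assumed because not stated: two-sided 5% test, no loss to endline.

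**Formulas.** Let f be the share of STAR control employment that remains, so p0 = 0.41 × f.
- Design effect: DE = 1 + (16 − 1) × ICC, giving 2.5, 4 and 7 at ICC 0.1, 0.2 and 0.4.
- SE = √{[p1(1 − p1) + p0(1 − p0)] × DE / (16 × 45)}.
- Power = Φ(|p1 − p0| / SE − 1.96).

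**Step 1: the plan's own claims, with p1 fixed at 0.53.**

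| ICC | f | p0 | Difference | SE | Power |
|---|---|---|---|---|---|
| 0.1 | 1.00 | 41% | 12.0 points | 0.0413 | 83% |
| 0.2 | 0.95 | 38.95% | 14.05 points | 0.0520 | 77% |
| 0.4 | 0.75 | 30.75% | 22.25 points | 0.0670 | 91% |

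The first and third claims are reproduced. The second falls slightly short of 80%; on this formula the threshold at ICC 0.2 is f of about 0.94. Pooled-variance and t-test versions also give 76–77%. A one-sided test would give 85%. The shortfall may come from reading a rounded value off Fig. 1, which was not available for this check.

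The third claim is met only with STAR+ held at 53%, which confirms how the factor was applied. At the 50% limit of the factor the implied difference is 53 − 20.5 = 32.5 points.

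**Step 2: the same control rate (30.75%) with other effects.**

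| Effect | STAR+ rate | ICC 0.1 | ICC 0.2 | ICC 0.4 |
|---|---|---|---|---|
| Plan: STAR+ fixed at 53% (22.25 points) | 53% | >99% | 99% | 91% |
| Constant 16 points | 46.75% | 98% | 88% | 67% |
| Constant 12 points | 42.75% | 85% | 66% | 44% |
| Constant risk ratio 0.53/0.41 = 1.29 (9 points) | 39.75% | 62% | 43% | 27% |

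The 16 points is the effect on labour market participation that Background and rationale cites for STAR. It may not be the same measure as the 53% and 41%.

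**Step 3: what a lower control rate does to power** (f = 1, 0.75, 0.5).

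| ICC | Constant 12 points | Constant risk ratio 1.29 |
|---|---|---|
| 0.1 | 83%, 85%, 91% | 83%, 62%, 40% |
| 0.2 | 63%, 66%, 74% | 63%, 43%, 27% |
| 0.4 | 41%, 44%, 50% | 41%, 27%, 17% |

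The direction depends on the scale on which the effect is held constant. At ICC 0.2 a 12-point effect stays below 80% at each control rate checked.

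**Step 4: minimum detectable difference.** Solving the power formula for 80% at p0 = 30.75% gives 11.2, 14.2 and 18.8 points at ICC 0.1, 0.2 and 0.4. At ICC 0.4 the STAR+ arm would have to reach 30.75 + 18.8 = about 49.5%.

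**The case against.** The strongest defence is that STAR+ is not STAR. Background and rationale says it was developed to address the gaps of STAR, and the Intervention section describes assistive devices, sensitisation events, accessibility audits and job matching. An effect larger among people with disabilities than in the general population fits that theory of change. The assumption is also open to view: the text names the arm that was scaled and the range, and makes the ICC 0.4 claim conditional on the control rate. The number of branches was limited by funding, so no other sample size was forgone.

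Much of this stands. A STAR+ rate near 53% is a legitimate scenario, but it is the only one used, and no reason is given for it. The condition attached to the ICC 0.4 claim concerns the control rate, not the STAR+ rate on which it equally depends.

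Two stronger readings are tempting. A reader might infer that a larger disability effect necessarily reduces power. That is so under a constant risk ratio; under a constant difference power rises slightly, and the document does not say which applies. A reader might also take the remark that "people with disabilities have been over-represented amongst the" programme's dropouts as evidence that STAR+ will achieve less. That remark concerns standard STAR, and the same section presents STAR+ as the response to it.

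**Conclusion.** The concern holds for the adequacy claims at ICC 0.2 and above and for the closing sentence. It does not show that the power claim as a whole is unsupported: at ICC 0.1 with an unreduced control rate the factor plays no part, and power is about 83%. The 22-point effect belongs to the ICC 0.4 scenario alone; it exceeds the 16 points cited for STAR, whereas the 14 points used at ICC 0.2 does not.

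With controls at 30.75%, 80% power needs about 14 points at ICC 0.2 and 19 points at ICC 0.4. A 12-point effect has 66% and 44% power there, and a constant risk ratio has 43% and 27%. These figures assume a two-sided 5% test, 45 clusters of 16 per arm and no loss to endline. Nor do they show that the trial is underpowered, because neither the ICC nor the true effect of STAR+ is known. They show that adequacy beyond an ICC of about 0.1 requires an effect larger than 12 points.

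**What to change.** Restate the sample size section, or set this out in the analysis plan that the article promises before endline:

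1. State the STAR+ arm employment rate assumed for youth with disabilities and give the reason for it.
2. Report power at ICC 0.1, 0.2 and 0.4 as the control rate falls, once with a constant absolute difference and once with a constant risk ratio. The 53% scenario can stay beside them if it is justified.
3. Give the minimum detectable differences: about 11, 14 and 19 points at a control rate of 31%.
4. State the significance level and sidedness, and recheck the ICC 0.2 claim at 95%.
5. Replace the closing sentence with one saying that 80% power for a 12-point effect is supported only at an ICC of about 0.1, and that higher ICCs need a larger effect.

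The cost is a recalculated figure and some rewording. Recruitment, outcomes and analysis do not change. The drawback is that the stated power becomes less favourable.

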**Fig. 1 Fig1:**
[figure not shown]
Sample size calculation

### Timeline

Baseline data collection is being conducted January-February 2022, in sync with recruitment. The process evaluation will be conducted at the end of STAR+ delivery. Endline data collection will take place approximately 17 months after the completion of STAR+ (approximately 24 months from baseline) to control for seasonal variations that can affect outcome measures.

### Data analysis

A detailed analysis plan will be published before the endline survey. The analysis will estimate intention-to-treat (ITT) effects of STAR+.

The quality of the balance achieved by randomisation will be assessed by describing the arms of the trial at baseline in terms of the primary and secondary outcomes and sociodemographic variables. If there is evidence of imbalance, based on subjective interpretation of the magnitude of the difference, such variables will be included *a priori* in the main analysis of the primary and secondary outcomes.

The effect of the intervention will be estimated by comparing the proportions (e.g. employment) and the means (e.g. earnings) between the arms of the trial. The unadjusted estimated effects will be reported as risk ratios for binary outcomes and difference in the means for continuous outcomes. In the final analysis, to increase the precision of the estimates and reduce the risk of bias from imbalances at baseline, regression will be used to adjust for the baseline levels of the outcome, stratification variables, and variables considered to be imbalanced at baseline. For binary outcomes, the risk ratio will be modelled with a modified Poisson regression model [29]. Linear regression will be used for continuous outcomes. A random mixed effect at the cluster level will be used to account for the clustered design.

In-depth interviews will be recorded, transcribed and translated. Detailed notes and transcripts will be analysed using thematic analysis. Coding frameworks will be developed using the semi-structured interview guides as a starting point. Additional codes emerging from the data will be incorporated into the framework in an iterative process. Transcripts and notes will be coded using NVivo 12. Codes will be grouped into themes and sub-themes. Comparisons and inter-relationships between themes and sub-groups (e.g. women vs men, by impairment type) will be conducted throughout the analysis. The process evaluation will also use data from the endline cRCT and monitoring data from BRAC on the receipt and user experience of different components of STAR+. This data will be tabulated and regression used to explore differences amongst STAR+ participants (e.g. by gender, location, impairment type).

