### Eligibility criteria

Participants in both the control and intervention arms must meet BRAC’s eligibility criteria for STAR+. Eligibility for STAR+ is based on the following conditions: (a) having a disability; (b) age is between 14 and 35 years; (c) dropped out of school for at least a year, (d) not currently in employment or training; and (e) currently living in poverty, meaning their household earns BDT 4000 (US$46) or less per capita per month.

Determining disability is methodologically complex, particularly for deciding programme eligibility [18, 19]. For STAR+, BRAC considers youth to have an eligible disability if they either have a disability identification card issued by the national government, or if they were identified in a door-to-door survey conducted in consultation with local Organisations of Persons with Disabilities (OPDs). Permanent residents can apply for disability identification cards, which involves a medical assessment to determine if they have a disability in line with the Persons with Disabilities Rights and Protection Act (2013) [20]. This legislation defines disability as including physical, sensory, intellectual, communication and psychosocial impairments, including specific conditions such as autism and Downs Syndrome [20]. The criteria used in the survey are aligned with UNCRPD and the national definitions of disability [21]. People with deafblindness and more severe intellectual impairments will not be part of the cRCT, as they will be included in specialised STAR+ pilot programmes that will be evaluated separately. All identified individuals will also be asked the Washington Group Short Set of questions [22]. These questions are widely used and the United Nations’ recommended questions for measuring disability prevalence in surveys to allow for international comparisons [23].

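### Extra covariates for the main analysis are picked by subjective reading of baseline imbalance, not by prognostic value, which works against the plan's own precision aim and leaves the final model open

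*Protocol article*

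**What the plan says.** The Data analysis section sets out four things.

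- Balance is to be assessed by "describing the arms of the trial at baseline in terms of the primary and secondary outcomes and sociodemographic variables". The sociodemographic variables are not listed.
- The selection rule reads: "If there is evidence of imbalance, based on subjective interpretation of the magnitude of the difference, such variables will be included". The same sentence gives the label and the place where they enter: "such variables will be included *a priori* in the main analysis of the primary and secondary outcomes".
- The final analysis will use regression to "adjust for the baseline levels of the outcome, stratification variables, and variables considered to be imbalanced at baseline". Two aims are given for this: better precision and less bias from baseline imbalance.
- "The unadjusted estimated effects will be reported as risk ratios for binary outcomes and difference in the means for continuous outcomes". The adjusted model is nevertheless the one described as final.

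The section opens with a commitment: "A detailed analysis plan will be published before the endline survey". It does not say that this plan will fix the covariate list or replace the imbalance rule.

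One entry condition under Eligibility criteria also bears on the point: "d) not currently in employment or training".

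**The concern.** The article does not merely leave a covariate list to a later document. It states a selection rule for the main analysis of the primary outcomes, and the rule is a poor one.

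In a randomised comparison, the precision gained by adjusting for a covariate depends on how strongly it predicts the outcome. Observed imbalance in a properly randomised trial is chance and says nothing about that. The rule therefore admits variables unrelated to employment or earnings that happen to differ, and leaves out strong predictors that happen to be balanced. That runs against the section's first stated aim.

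The rule is also only loosely a priori. It sets no threshold, no candidate list and no date by which the judgement must be closed. Two careful analysts could follow it and fit different final models.

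The open part of the model matters more than usual for employment. The baseline level of the outcome is always included, but participants had to be out of work to qualify, so that term should vary little. Beyond the stratification by division, the subjectively chosen variables may be most of the useful adjustment.

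**Working it through.** The plan gives no figure on this point to reproduce. The check asks how many covariates the rule would flag by chance, what that costs in precision, and whether it affects type I error.

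**Inputs from the protocol article.** 45 intervention and 46 control clusters (Design); 16 participants per cluster and ICCs of 0.1 and 0.2 (Sample size).

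**Assumptions.** 6 or 12 candidate covariates, each standardised and clustered like the outcome; together they explain 10% or 30% of outcome variance, in equal shares; two-sided 5% test; imbalance cut-offs from 0.05 to 0.25 SD.

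**Step 1. Chance imbalance.** The SD of a covariate's between-arm difference, in SD units, is √{[ICC + (1 − ICC)/16] × (1/45 + 1/46)}.

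- ICC 0.1: √(0.15625 × 0.04396) = 0.083.
- ICC 0.2: √(0.25 × 0.04396) = 0.105.

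The chance of being flagged at cut-off h is 2 × [1 − Φ(h/SD)]. Multiplied by 12 candidates:

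| Cut-off (SD) | Flagged, ICC 0.1 | Flagged, ICC 0.2 |
|---|---|---|
| 0.05 | 6.6 | 7.6 |
| 0.10 | 2.7 | 4.1 |
| 0.15 | 0.8 | 1.8 |
| 0.25 | 0.03 | 0.2 |

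Simulation gave the same counts to within 0.1. The final model could thus hold anything from none to more than half of the candidates, depending on an unstated threshold.

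**Step 2. Precision.** If a fixed set explains a share R² of the outcome variance, the standard error is multiplied by about √(1 − R²): √0.9 = 0.949 or √0.7 = 0.837. This ignores the cost of estimating the coefficients, which is a reason to keep the list short. At a cut-off of 0.10 SD and ICC 0.1, each covariate enters with probability 0.228. With equal prognostic shares, the rule then removes on average 0.228 × 30% = 6.8% of the variance, where the full set removes 30%.

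**Step 3. Type I error.** Null simulation, linear regression on cluster means, 4000 runs per scenario. The Monte Carlo standard error at 5% is √(0.05 × 0.95/4000) = 0.34 percentage points.

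| Analysis | False positives across scenarios |
|---|---|
| All candidates, fixed in advance | 4.5% to 5.3% |
| One cut-off (0.10 SD), blind to outcome | 3.0% to 4.8% |
| Most favourable of five cut-offs, outcomes seen | 6.4% to 7.5% |

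The second row is conservative because the covariates left out are by construction nearly balanced. The estimate therefore varies less than its model-based standard error implies. The 3.0% values occur with 12 covariates and R² = 30%.

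**Step 4. Movement of the estimate.** Across the five cut-offs, the highest and lowest adjusted effects differ on average by 0.03 to 0.07 SD. Against the unadjusted standard errors in Step 1 (0.083 and 0.105), that is roughly a third to nearly two thirds of a standard error (0.030/0.083 = 0.36; 0.066/0.105 = 0.63).

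**The case against.** The strongest defence is timing. Baseline data were collected in January and February 2022, and the Timeline section puts endline about 24 months after baseline. A plan published before endline can record the imbalance judgement before any outcome exists. On that reading, a priori means before outcome data: loose wording, not a contradiction. This stands, with one gap: the article does not say that the plan will lock the list.

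The defence can add that much of the model is already fixed. Baseline outcome and stratification variables always enter, and unadjusted effects are reported, so a reader could see any shift caused by the chosen covariates. This also stands, though it is weaker for employment, where the baseline term should carry little information.

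Two stronger readings are tempting, and the documents support neither. First, a reader might infer that the nominal 5% error fails. The stated rule selects on baseline differences, not on results, and Step 3 shows no inflation when it is applied blind to outcome. Second, a reader might infer that the judgement will be unmasked because the research team generated the allocation. The article does not say who will judge imbalance or whether arm labels will be visible. A judgement closed before endline could not be steered by results in either case.

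Nor does the article show which covariates are the right prognostic set. That choice belongs to the investigators.

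**Conclusion.** The point holds as a badly fixed analysis rule. Choosing covariates by subjective reading of chance imbalance ignores prognostic strength, sits uneasily with the a priori label and forgoes precision, most of all for employment. It also leaves the final model open, by an average of about a third to nearly two thirds of a standard error across plausible cut-offs.

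It is not a demonstrated loss of type I error control. Used before endline and blind to outcome, the rule is if anything conservative. Error rises to about 6% to 8% only if the judgement is made or revised with endline data in view, which the article neither describes nor excludes.

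The figures rest on assumed ICCs, covariate numbers, prognostic strength and cut-offs. They come from a linear cluster-mean model, not the planned modified Poisson model, and the simulation did not include the baseline outcome or division. They show direction and rough size. The argument about prognostic strength does not depend on them.

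**What to change.** In the analysis plan promised before endline:

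1. Remove the imbalance rule from the main analysis.
2. Name a short list of baseline covariates that the investigators expect to predict employment and earnings (for example sex, age, impairment type and functional severity). Include them whatever the observed balance, alongside the baseline outcome and division.
3. Report baseline balance descriptively only.
4. Put any adjustment for observed imbalance in a labelled sensitivity analysis.

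The cost is wording. The baseline questionnaire covers demographics and household finances, and the Washington Group questions are asked of everyone identified. Gender and impairment type already feature in the subgroup objective. No new data collection and no design change are needed.
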